#### Design of the protocol

2.11.3

This study employed a prospective randomized double-blind RCT design, validated against international CONSORT guidelines. The randomization process is implemented through a computer-generated block randomization sequences. Participant allocation was executed by an independent statistician through an Interactive Web Response System (IWRS), ensuring allocation concealment until intervention initiation. A blind design (masking both investigators and participants) was implemented, with primary endpoints adjudicated by a blinded endpoint committee.

#### Strict participant eligibility criteria

2.11.4

Implementing stringent inclusion criteria is a critical method for controlling bias. By establishing well-defined inclusion and exclusion criteria, the study population can be rigorously confined to a specific range, reducing heterogeneity among participants and facilitating objective conclusions regarding the observed factors.

#### Blinding implementation and outcome assessment

2.11.5

Blinding procedures mitigate measurement bias and expectation bias by preventing awareness of intervention assignments among investigators and participants. This study implemented a three-tier blinding system: (1) Participant blinding (using sham stimulation and blinded the display screen); (2) Investigator blinding (group allocation concealed via central randomization system); (3) Statistician blinding (de-identified raw data processing). Primary endpoints were assessed by an independent Endpoint Adjudication Committee using standardized scales (e.g., NIHSS scores) under blinded conditions, with committee members excluded from trial operations and denied access to allocation databases.

#### Laboratory quality assurance

2.11.6

All biomarker assays strictly adhered to ISO 15189:2022 medical laboratory standards, implemented through the “Clinical Biochemical Testing Standard Operating Procedures” (WS/T 641–2023). According to experimental quality control protocols, laboratory test results must be documented through computer-generated printouts to prevent data inaccuracies caused by human errors.

#### Research training measures and methods

2.11.7

To ensure the smooth progress of the research, specialized clinical training sessions must be organized by the project team prior to the commencement of clinical trials. These sessions aim to provide uniform training for clinical researchers, including detailed instruction on the project implementation plan and operational procedures. Through these trainings, researchers are required to achieve comprehensive familiarity with the entire research process and specific implementation guidelines. This approach enhances intra-observer consistency and inter-observer consistency among researchers, thereby ensuring the reliability of clinical research conclusions.

#### Participant compliance management measures

2.11.8

To enhance compliance and reduce participant attrition, the following strategies were implemented:

Ethical principle: Adherence to voluntary participation was ensured through signed informed consent forms.

Healthcare optimization: Patient retention was promoted by improving healthcare quality, treatment environment, and cost transparency to encourage continuous participation.

Physician-patient communication: Detailed explanations of diagnostic tests, therapeutic procedures, and follow-up requirements were provided to foster cooperation.

Contact documentation: Comprehensive contact information (including emergency contacts) was recorded for follow-up purposes.

Symptom monitoring: Participants received standardized symptom diaries with training on grading scales (e.g., Visual Analog Scale) to document disease progression and adverse events.

Treatment protocol compliance: Explicit instructions prohibited concomitant medications during the study. Completed symptom diaries were reviewed with participants at study closure to verify data accuracy.

#### Data management quality control

2.11.9

Standardized personnel training, optimized questionnaire logic, and double-blind data entry protocols were implemented to enhance data completeness and accuracy, significantly reducing error rates and ensuring research outcome reliability.

#### Data entry staff training

2.11.10

The study implemented a rigorous selection protocol for data verification and entry specialists, requiring candidates to hold at minimum a bachelor’s degree in medical sciences (including current master’s students) while demonstrating both professional responsibility and fundamental computer literacy. Selected personnel underwent systematic pre-service training encompassing five critical domains: questionnaire design rationale, database architecture, standardized coding protocols, data entry operational guidelines, and quality control specifications. This training program concluded with formal competency assessment and certification by an independent academic committee.

To ensure procedural standardization and data consistency, a dual-blind pilot verification and preliminary data entry phase was conducted prior to formal operations. This preparatory phase served to reinforce operational standardization through simulated practice while establishing unified quality evaluation benchmarks aligned with international research protocols.

## Discussion

3

As a prevalent circadian rhythm sleep–wake disorder, CI has been shown to significantly impair quality of life, cognitive performance, and emotional regulation in affected individuals (28). While cognitive behavioral therapy for insomnia (CBT-I) remains the first-line intervention per international guidelines, its implementation faces substantial challenges including prohibitive healthcare costs, low adherence and shortage of certified therapists (29). Benzodiazepine receptor agonists (BZRAs), though effective in reducing sleep onset latency in short-term use, carry significant iatrogenic risks: withdrawal syndromes, dose-dependent daytime somnolence, cumulative cognitive impairment, and potential for misuse (30). Consequently, novel non-invasive neuromodulation techniques are emerging as promising alternatives, demonstrating superior safety profiles and precise targeting capabilities (31).

FD is a gastrointestinal dysfunction disorder characterized by chronic duration and persistent or recurrent upper abdominal symptoms, with rising incidence yet incompletely understood pathogenesis. Patients with overlapping somatic symptoms often exhibit aggravated clinical manifestations and diminished quality of life (32). Current therapeutic strategies designate proton pump inhibitors (PPIs) and H2 receptor antagonists as first-line treatments for epigastric pain syndrome (EPS), while prokinetic agents are preferred for postprandial distress syndrome (PDS). However, both approaches demonstrate suboptimal response rates and high recurrence (33). Notably, the adverse effects associated with long-term use of prokinetics, acid suppressants, and neuromodulators further compound the complexity of clinical management (34).

Chronic low-grade inflammation is implicated as a potential pathogenic pathway in CI. Patients with insomnia and shortened sleep duration exhibit elevated systemic C-reactive protein (CRP) levels, correlating with chronic inflammatory states (35). Reduction of proinflammatory cytokines has been shown to alleviate insomnia symptoms (36). Notably, low-grade inflammation also contributes to functional dyspepsia pathogenesis. Dyspeptic patients demonstrate low-grade duodenal mucosal inflammation (37), and attenuation of mucosal inflammation correlates with symptom improvement (38). Preclinical studies reveal that activation of the NF-κB signaling pathway and increased interleukin-6 (IL-6) levels in the duodenal mucosa characterize dyspepsia model rats, indicative of mucosal inflammation (39). Anti-inflammatory interventions in these models restore body weight, food intake, and small intestinal motility. Collectively, low-grade inflammation represents a shared pathogenic mechanism in CI and FD, positioning mucosal inflammation reduction as a potential therapeutic target for their comorbidity.

Enhanced vagal nerve activity serves as a critical therapeutic pathway for mitigating low-grade inflammation. Vagus nerve stimulation significantly reduces proinflammatory cytokine expression (40), and further mediates the downregulation of interleukin-6 (IL-6) in the duodenal mucosa of dyspeptic patients, correlating with decreased symptom severity indices (41). As a key immunoregulatory component, the vagus nerve modulates macrophage polarization to exert anti-inflammatory effects, which are abolished following surgical vagotomy (42). Experimental evidence demonstrates that vagal stimulation suppresses proinflammatory cytokine production in immature macrophages (39). In functional dyspepsia (FD) model rats, auricular vagus nerve stimulation downregulates serum interleukin-1β (IL-1β) levels, reduces visceral hypersensitivity, and alleviates dyspeptic symptoms (43). These findings collectively indicate that vagal neuromodulation attenuates low-grade inflammation through targeted cytokine suppression.

Clinical studies demonstrate that taVNS at varying intensities significantly reduces insomnia severity. A randomized controlled trial by Zhang et al. (44) revealed that taVNS (intensity: 0.8–1.5 mA, frequency: 4/20 Hz, pulse width: 200 μs) decreased Pittsburgh Sleep Quality Index (PSQI) scores in insomnia patients, accompanied by improved sleep quality, shortened sleep latency, and prolonged total sleep duration. Further validation by Wu X et al. (45) indicated that continuous taVNS intervention (intensity: 7–12 mA, frequency: 20 Hz, pulse width: 200 μs) significantly reduced neuronal activity in sensorimotor networks (right cerebellum, right medial superior frontal gyrus, and bilateral supplementary motor areas), with PSQI improvements surpassing those of the control group. In a randomized, double-blind, controlled trial, Dos Reis et al. (46) administered 20-min left-ear taVNS (20 Hz) and observed its positive effects on stress reduction and sleep quality enhancement. Research highlights the concha cymba as a potential optimal stimulation site for taVNS (47), yet no clear consensus exists regarding standardized reporting criteria. Current parameter combinations (frequency: 80 Hz, pulse width: 100 μs, duration: 40–60 s) require further clinical validation, though their multi-target regulatory effects on sleep–wake circuitry are mechanistically supported.

A randomized controlled trial demonstrated that 4-week twice-daily taVNS at 10 Hz or 25 Hz significantly improved symptom response rates and adequate relief rates in adults with Rome IV-defined functional dyspepsia compared to sham stimulation, with sustained efficacy through 12-week follow-up and no significant difference between frequencies, while exhibiting low adverse event incidence (48). The taVNS alleviates gastrointestinal dysfunction in patients with postprandial distress syndrome (49). Evidence indicates that auricular-vagal stimulation improves symptoms including early satiety, postprandial bloating, epigastric fullness, abdominal pain, heartburn, and nausea-vomiting in dyspeptic populations (50, 51), while enhancing quality of life, reducing anxiety-depressive comorbidity, and maintaining sustained therapeutic effects without adverse events. Mechanistically, taVNS enhances vagal efferent signaling to ameliorate dyspeptic symptoms (52), significantly lowering symptom severity scores and elevating quality-of-life indices, with durable long-term efficacy.

The taVNS demonstrates efficacy in ameliorating CI and comorbid dyspeptic symptoms without adverse effects, representing a promising therapeutic strategy for geriatric patients with overlapping CIa and FD, mechanistically linked to vagal-mediated modulation. Both CI and FD share immunoinflammatory pathogenic pathways (53), with clinical symptom alleviation observed following reduced inflammatory cytokine expression (54–56). Insomnia has been identified as a potential marker of subclinical inflammatory activity (57). While inflammation reduction is critical for treating CI comorbid with FD, the underlying mechanisms remain incompletely elucidated.

Accumulating evidence indicates that low-grade inflammatory status may serve as the fundamental pathological mechanism underlying the comorbidity of chronic insomnia and functional dyspepsia. Although current clinical research on taVNS has primarily concentrated on individual disorders, our preliminary clinical investigations have demonstrated its synergistic therapeutic efficacy in patients with comorbid chronic insomnia and functional dyspepsia, thereby providing direct clinical substantiation for this pathophysiological hypothesis. By implementing longitudinal monitoring of dynamic fluctuations in peripheral inflammatory markers and central neurotransmitters throughout taVNS intervention, this study systematically deciphers the bidirectional regulatory pathways of the auricular vagus nerve in peripheral immune modulation and central neurochemical equilibrium, yielding novel mechanistic evidence to elucidate the multimodal integrative regulatory functions of the vagus nerve.

This randomized double-blind sham-controlled trial comprised an active group receiving taVNS at the concha cymba (frequency: 80 Hz, pulse width: 100 μs, pulse 40–60s) for 30 min per session, 5 sessions weekly for 3 consecutive weeks, alongside the sham group undergoes identical procedures with non-active electrodes. Primary endpoints included variations in the PSQI and NDSI, with secondary outcomes encompassing ISI, SF-36, serum biomarkers (pro-inflammatory cytokines IL-1*β*, IL-4, IL-6, TNF-*α*, hs-CRP, TGF-β) and neurotransmitters (DA, 5-HT, NE, Glu, GABA). Should the trial demonstrate statistical superiority of taVNS over sham in both symptom domains, it will not only elucidate the neuroimmune axis mechanism underlying comorbid CI with FD in elderly patients (e.g., vagus nerve-mediated duodenal mucosal inflammatory regulation), but also propose a novel non-pharmacological intervention characterized by precision targeting, elevated safety, and optimal adherence, thereby establishing a neuromodulation-based integrative therapeutic strategy for geriatric comorbidity management.

This study acknowledges limitations inherent to its exploratory design. The modest sample size reflects both the prospective nature of the trial and stringent inclusion criteria for CI comorbid with FD. Although preliminary clinical evidence suggests the therapeutic efficacy of high-frequency taVNS, the absence of prior literature supporting this intervention introduces potential bias and elevates uncertainty in evidence quality. Current taVNS protocols lack expert consensus regarding optimal stimulation parameters (frequency, intensity, site), and resource constraints precluded comparative effectiveness analyses across parameter combinations. Furthermore, the absence of objective neuroimaging or electroencephalographic biomarkers in outcome measures may introduce measurement bias. These limitations will be systematically addressed in subsequent validation studies.

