**Methods/design:**

This double-blind randomized controlled trial will enroll 60 elderly patients (60–85 years) meeting ICSD-3 criteria for CI and Rome IV criteria for FD. Using block randomization with computer-generated sequences, eligible participants will be allocated 1:1 to either active taVNS group (*n* = 30) or sham control group (*n* = 30). The CFDA-certified transcutaneous vagus nerve stimulator (Model tVNS501, Reach Medical, China; Registration No. SuXieZhun20212090050) will be positioned at standardized anatomical sites: the concha cymba (the inferior margin of the intersection between the superior and inferior crura of the antihelix within the cymba conchae), electrical stimulation will deliver with fixed parameters (frequency: 80 Hz, pulse width: 100 μs, pulse 40–60s). The active group will receive validated taVNS parameters, while the sham group will undergo identical procedures without electrical output. Interventions will be administered 30 min per session, 5 sessions weekly for 3 consecutive weeks. Primary endpoints include changes in Pittsburgh Sleep Quality Index (PSQI) and Nepean Dyspepsia Symptom Index (NDSI) at week 3. Secondary outcomes encompass Insomnia Severity Index (ISI), 36-Item Short Form Survey (SF-36), and serum biomarkers (pro-inflammatory cytokines IL-1*β*, IL-4, IL-6, TNF-*α*, hs-CRP, TGF-β; neurotransmitters Dopamine (DA), serotonin (5-hydroxytryptamine, 5-HT), norepinephrine (NE), Glutamate (Glu), *γ*-aminobutyric acid (GABA)). Safety profiles will be systematically evaluated using CTCAE v5.0 criteria, with all adverse events documented throughout the study.

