**Discussion:**

This study mitigate the adverse effects associated with the significant side effects of oral medications in elderly patients with CI comorbid with FD. It seeks to scientifically validate the clinical efficacy of taVNS therapy, elucidate its underlying anti-inflammatory and neuromodulatory mechanisms, and establish a multimodal evidence chain integrating “efficacy-inflammation-neuromodulation.” By doing so, this research provides a novel, convenient, scientifically validated, effective, and safe non-pharmacological therapeutic approach for elderly patients with CI and FD, it offers innovative insights and methodologies for the development of pharmaceuticals, medical devices, and related products.

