Currently, pharmacological treatments for CI in the elderly are associated with systemic risks. Studies have shown (11–14) that the risk of dependence on benzodiazepines is 34.7% (OR = 3.2, 95%CI 2.1–4.9), and the incidence of withdrawal syndrome after discontinuation is 28.4% (RR = 2.8). Additionally, a significant dose ineffectiveness threshold effect has been observed, necessitating off-label dosing in some patients, while 12.7% of patients exhibit a decline in estimated glomerular filtration rate (eGFR), and the incidence of hepatorenal toxicity is ≥30%. The treatment of FD lacks targeted therapies and effective drugs, with proton pump inhibitors (PPIs) showing a clinical response rate of only 38.2% (95%CI 32.7–44.1), and long-term use of prokinetic agents increases the risk of QT interval prolongation (HR = 1.68) (15, 16).

When CI and FD coexist, the risk of drug interactions increases by 71% (*p* < 0.001) (17), and the cost-effectiveness ratio of conventional therapies is as high as $152,300 per quality-adjusted life year (QALY) (18). Therefore, there is an urgent need for reliable, safe, cost-effective, and efficient clinical treatment options for elderly patients with CI comorbid with FD. In this context, taVNS emerges as a novel therapeutic approach, offering a potential innovative solution for this patient population.

This study will systematically evaluate the clinical efficacy of transcutaneous auricular vagus nerve stimulation (taVNS) in elderly patients with CI comorbid with FD. By analyzing dynamic fluctuations in inflammatory cytokines and neurotransmitters, we will objectively validate the clinical effectiveness of taVNS in geriatric comorbidity management for the first time. The investigation will further elucidate the vagus nerve-mediated regulatory mechanism of duodenal mucosal inflammation and establish a novel non-pharmacological intervention characterized by precision targeting, high safety profile, and enhanced therapeutic compliance, which will provide a theoretical foundation for developing neuromodulation-based integrated therapeutic strategies for elderly patients with multimorbidity management.

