### Intervention

2.7

Following standardized screening, all participating clinicians underwent unified training in both taVNS and sham taVNS protocols. The informed consent form explicitly stated that the study involved two distinct neuromodulation interventions (which may differ in electrical sensation and therapeutic responses). Training modules included: (1) Device operation: standardized procedures for power cycling and locked parameter interfaces; (2) Anatomical localization: precise electrode placement at the tragus: the inferior margin of the intersection between the superior and inferior crura of the antihelix within the cymba conchae and the junction of the inferior crus of the antihelix and the auricle within the cymba conchae using auricular anatomical charts; (3) Blinding maintenance: standardized communication protocols to prevent unintentional disclosure of group allocation. All interventions were conducted in standardized treatment rooms within the hospital inpatient department.

All clinicians participating in this study were required to have at least 2 years of standardized acupuncture practice. Participants were placed in a supine position, and the auricular stimulation areas were cleaned with 75% ethanol solution followed by placement of ear clips. The clinically trained operator, blinded to group assignment, using transcutaneous auricular vagus nerve stimulators (tVNS501), precisely placed bipolar electrodes at standardized anatomical sites: the concha cymba (the inferior margin of the intersection between the superior and inferior crura of the antihelix within the cymba conchae). The intervention protocol consisted of 30-min sessions, administered weekdays from 9:00 to 11:00 AM for three consecutive weeks (15 sessions total).

Participants shall be withdrawn from the trial and provided with appropriate medical interventions under any of the following circumstances: (1) occurrence of serious adverse events; (2) voluntary withdrawal request from the participant; (3) clinical deterioration of the underlying condition; (4) requirement for prioritized treatment of other medical disorders; or (5) development of localized irritation or allergic reactions.

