#### Statistical analysis

2.9.3

Incidence rate: AE incidence = (Number of AE episodes / Total treatment sessions) × 100%.

Severity stratification:

Grade 1–2: Mild, requiring no intervention.Grade ≥ 3: Mandating medical intervention or protocol modification.

Temporal analysis: Time-to-event analysis using Cox proportional hazards model.

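### Superiority on PSQI and NDSI cannot support the safety and adherence conclusion that the Discussion attaches to it, and the stated safety analysis does not fill the gap

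*Protocol article*

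**What the plan says.** In section 3 (Discussion) the condition is "Should the trial demonstrate statistical superiority of taVNS over sham in both symptom domains". What follows from it includes a mechanistic claim and then "but also propose a novel non-pharmacological intervention characterized by precision targeting, elevated safety, and optimal adherence". No adverse-event, withdrawal or session-completion result is part of the condition.

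Two other places state the same qualities in advance:
- Abstract, Discussion: "this research provides a novel, convenient, scientifically validated, effective, and safe non-pharmacological therapeutic approach".
- Section 1 (Background), as an aim: "establish a novel non-pharmacological intervention characterized by precision targeting, high safety profile, and enhanced therapeutic compliance".

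Section 3 also summarises prior evidence in these terms: "The taVNS demonstrates efficacy in ameliorating CI and comorbid dyspeptic symptoms without adverse effects".

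The trial does collect safety data. The Abstract promises CTCAE v5.0 grading "with all adverse events documented throughout the study". Sections 2.9.1 and 2.9.2 set observation windows, SAE reporting and causality assessment. Section 2.10 sets up a DSMB. Section 2.9.3 gives the summary statistic as "AE incidence = (Number of AE episodes / Total treatment sessions) × 100" percent, plus a Cox model. Section 2.8.5 assigns the safety analysis to a modified per-protocol set that keeps participants who stopped because of adverse events.

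Adherence appears only in section 2.8.5, where completing 80–120% of the dose is a per-protocol criterion. It is not among the outcomes in sections 2.8.2 and 2.8.3. On the setting, section 2.7 says: "All interventions were conducted in standardized treatment rooms within the hospital inpatient department".

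**The concern.** The conclusion does not follow from its condition. A lower PSQI and NDSI on active stimulation says nothing about how many participants were harmed or how many would keep up the treatment. The condition could be met with few adverse events or with many.

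The stake is what the results paper may claim for patients aged 60 to 85. The Abstract and Background present taVNS as the safer option beside oral drugs, so a sentence published in advance that ties safety to two symptom comparisons is easily repeated once those comparisons succeed. If the safety summary is then a small per-session percentage, it will seem to confirm a claim that the data cannot carry.

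**Working it through.** **1. What the sample size was built for.** Section 2.5 uses 20% versus 70% efficacy, α = 0.05 and power 0.99. The unpooled two-sided formula gives (1.960 + 2.326)² × (0.2×0.8 + 0.7×0.3) / 0.5² = 27.19, so 28 per group, which matches the protocol; 30 are enrolled. No safety or adherence quantity enters this calculation, and the document gives no figure for either.

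**2. Condition against conclusion.**

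| Claimed | In the condition? | What the design offers |
|---|---|---|
| Efficacy on both scales | Yes | Randomised comparison with sham |
| Safety | No | Graded adverse events in a separate analysis; the only comparator is a sham without current |
| Adherence | No | No listed outcome; dose completion is only a per-protocol filter; supervised hospital sessions |

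There is no drug arm, so nothing can be shown about safety relative to oral medication. Operators deliver every session in hospital, so sessions completed will largely reflect that setting.

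**3. The per-session rate.** Each arm has 30 participants × 15 sessions = 450 sessions if all are completed. As an illustration (the event counts are assumed):
- 9 participants with one episode each: 9/30 = 30% of participants, 9/450 = 2% per session.
- 1 participant with nine episodes: 1/30 = 3.3% of participants, again 9/450 = 2% per session.

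The statistic is the same in both cases. With one episode per affected participant, it is one fifteenth of the participant-level risk.

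**4. The safety population.** The modified per-protocol set restores participants who discontinued because of adverse events. It is not said to restore those excluded for other reasons, such as prohibited medication, visit deviations or low dose completion. The lower dose limit is 0.80 × 15 = 12 sessions. A participant who stops at 11 sessions for a reason not recorded as an adverse event could be left out, along with any events already experienced.

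**5. What 30 active participants can exclude.** With zero events, the exact 95% upper bound is:
- one-sided: 1 − 0.05^(1/30) = 0.095, or 9.5%;
- two-sided: 1 − 0.025^(1/30) = 0.116, or 11.6%.

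If only 27 were analysed (10% loss, the upper end of the dropout assumed in section 2.5), the bounds would be 10.5% and 12.8%.

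**The case against.** The strongest reply is that this is one forward-looking, promotional sentence whose verb is to propose. No analysis section derives safety from PSQI or NDSI, and no test, dataset or sample size depends on the sentence. That stands. A reader might infer that the protocol contains a decision rule that declares taVNS safe even when the active arm is harmed, and might relabel efficacy power as the chance of a false safety claim. The documents do not support this. Safety is assessed separately, the DSMB has SAE and dropout triggers, section 2.7 withdraws participants for several kinds of adverse event, and nothing says these results would be ignored. Efficacy power is not a measure of this fault. It would likewise be wrong to say that the trial has no safety or adherence data.

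A second reply is that the safety adjective in section 3 may simply mean high, as in the Background, without any comparison. That is fair for that sentence. The drug comparison comes from the Abstract and Background, which set the treatment against the risks of medication.

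A third is that participant-level tables and intervals belong in the SAP. Their absence alone would be no finding. But the article does state a safety statistic and a safety population, and both are poorly suited to the claim.

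A fourth is that section 3 concedes an exploratory design and a modest sample. It does, but the limitations listed there mention neither safety nor adherence, so they do not qualify the claim.

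**Conclusion.** The point holds as a fault in the stated conclusion and in the safety analysis that would have to support it. Superiority on both scales would justify an efficacy statement and nothing about safety or adherence. The per-session rate can show 2% where 30% of participants had an event, and the safety set need not contain everyone treated. With 30 active participants, even a clean record excludes only event rates above 9.5% (one-sided) or 11.6% (two-sided).

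The bounds rest on all 30 active participants being observed. The dilution example rests on full session completion and on assumed event counts. The efficacy analysis and the sample size are unaffected, and the weight is modest. The change is still worth making because it alters what the trial may conclude and uses data already collected.

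**What to change.** - **Section 3.** Limit what follows from superiority to efficacy: taVNS improves PSQI and NDSI more than sham at week 3. Remove the safety and adherence wording from that conditional.
- **Abstract and section 1.** Remove the matching wording: safety in both places, and compliance in the Background.
- **Sections 2.9.3 and 2.8.5.** Base any safety statement on the number of participants with at least one adverse event, SAE or withdrawal for an adverse event, by arm, in everyone treated. Give exact 95% confidence intervals and the active-minus-sham risk difference with its interval. Word the result as the event rate that the data exclude.
- **Adherence.** Report sessions completed by arm and describe it as adherence under supervised hospital delivery.
- **Drug therapy.** Make no safety comparison with it.

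The cost is a few wording edits and one small table, with no extra participants or procedures. The downside is a less favourable headline.
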